### Implementation {16c}

The allocation sequence will be generated with the Graphpad tool by a member of the research team. Enrollment will be carried out by medical doctors. Once included, participants will receive the prescription for the first FSH injection dose, whether decided by the clinician or IDoser, and self-administer it as indicated by their clinician.

## Assignment of interventions: blinding

### Who will be blinded {17a}

Participants will be blinded to arm allocation. The research team will also be blinded, with the exception of the data coordinator. The medical team, with the exception of the ones assigned to care for the participants, will also be blinded to arm allocation. The embryology laboratory team will also be blinded.

### Procedure for unblinding if needed {17b}

Unblinding for participants will be permissible after their participation in the trial is ended. Additionally, it will be permissible for patients and the medical and embryology team in the event of a medical event that justifies unblinding.

## Data collection and management

### Plans for assessment and collection of outcomes {18a}

All trial data will be collected as per standard clinical practices for IVF/ICSI treatments in the participant clinics.

### Plans to promote participant retention and complete follow-up {18b}

There are no additional plans for retention of participants.

### Data management {19}

Data will be registered both in the electronic data table where allocation is provided and in a separate registry file. In the electronic data base, maximum and minimum value checks will be performed for every variable (if applicable).

### Confidentiality {27}

Participants’ information will be stored in both an electronic data table and registry file in a secure folder with controlled access only accessible to clinicians and the research team involved in the trial. This folder will be located in a secure server under exclusive control of the sponsor. Both the data table and registry file will be password protected. All data will be anonymized. Personal data will be protected according to the Regulation (EU) 2016/679 of the European Parliament and the Council of 27th April 2016 on the protection of natural persons in regards to processing of personal data and on the free movement of such data (General Data Protection Regulation or GDPR). In Spain, in addition to the GDRP, the transposition of this regulation to the national “Ley Orgánica 3/2018, de 5 de diciembre, de Protección de Datos Personales y garantía de los derechos digitales” will apply.

Relevant data will be stored 10 years after the finalization of the trial as per Regulation (EU) 2017/745 from the 5th of April.

### Plans for collection, laboratory evaluation, and storage of biological specimens for genetic or molecular analysis in this trial/future use {33}

Not applicable as no biological specimens will be retrieved during this trial for any genetic or molecular analysis; only data will be registered for the purposes of this specific trial.

## Statistical methods

### Statistical methods for primary and secondary outcomes {20a}

#### Descriptive analysis

Description of all demographic and result variables included in the trial will be provided overall and per study group (mean, standard deviation or SD, *n*, $$\%$$).

#### Univariable analysis

Differences regarding the number of MII oocytes amongst the groups will be evaluated using Student’s *t* test or Mann-Whitney *U* test (if the distribution is not normal). These tests will also be used to compare FSH doses and COC number.

Regarding all categorical variables (OHSS risk, OPU cancelation, cycle cancelation, clinical pregnancy, live birth), differences between groups will be evaluated using Pearson’s chi-squared. Description of adverse events (if any) will be provided by the study group.

Alpha risk is set at a 5% for the primary analysis, focusing on the difference between MII oocytes retrieved between the two arms of the study. For secondary and subgroup analysis, appropriate statistical adjustment methods will be implemented.

All analyses will be performed using Python version 3.7.6. A *p*-value < 0.05 will be considered as statistically significant.

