### Objectives {7}

This RCT tests the hypothesis that the performance of IDoser in prescribing the initial dose of FSH during COS is not inferior to the performance of a clinician in the average number of mature oocytes retrieved. Secondary objectives include the effect of IDoser on number of cycle cancelations (due to low response or no retrieval of oocytes), number of cases with OHSS risk, clinical pregnancy, and live birth per first transfer.

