### Trial design {8}

The trial design is a single-blinded RCT with two arms with a 1:1 allocation ratio, comparing outcomes following FSH dose selection by IDoser and dosing based on standard clinical practice.

The hypothesis that will be tested is whether the performance of IDoser selecting the first dose of FSH is non-inferior to the standard clinical protocol in regards to the average number of mature oocytes recovered per group. The difference in the number of MII that is regarded to be clinically significant is 2 MII. Our decision to consider a difference of two MII oocytes as clinically significant is based on empirical evidence and clinical relevance. As only 30 to 40% of inseminated mature oocytes develop into blastocysts [13, 14], the choice of two MIIs strikes a balance between statistical significance and clinical practicality, while taking into account the consequent impact on the success of fertility treatments. If the average number of MII in the intervention group is inferior in 2 or more units, IDoser will be considered inferior to the standard clinical practice.

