### Sample size {14}

A sample size calculation was performed to establish the number of participants required for the study. To determine a statistically significant difference equal or greater to 2 MII oocytes, 118 subjects are necessary in each group (*n *= 236), accepting an alpha risk of 0.05 and a beta risk of 0.2 in a one-sided test. We estimate a mean common standard deviation of 5.84 (as per the observational data included during development and validation of IDoser) and anticipate a drop-out rate of 10%.

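### The primary analysis tests for a difference without the 2-MII margin, and the one rule that uses the margin ignores sampling error, so the non-inferiority hypothesis is not tested

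*Protocol article*

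**What the plan says.** Objectives {7} sets the hypothesis that IDoser "is not inferior to the performance of a clinician in the average number of mature oocytes retrieved". Trial design {8} supplies the margin: "The difference in the number of MII that is regarded to be clinically significant is 2 MII". The same section gives the only rule that uses it: "If the average number of MII in the intervention group is inferior in 2 or more units, IDoser will be considered inferior" to standard practice.

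Sample size {14} arrives at 118 per arm, "accepting an alpha risk of 0.05 and a beta risk of 0.2 in a one-sided test", with an SD of 5.84 and 10% drop-out. It words its target as follows: "To determine a statistically significant difference equal or greater to 2 MII oocytes".

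The analysis is fixed under Univariable analysis in {20a}: "Differences regarding the number of MII oocytes amongst the groups will be evaluated using" Student's t test, or Mann-Whitney U when the data are not normal. The same tests are then assigned to FSH dose and COC number. The section adds: "Alpha risk is set at a 5% for the primary analysis, focusing on the difference between MII oocytes retrieved between the two arms". A p-value below 0.05 "will be considered as statistically significant". It states no margin, shifted null, confidence limit or side.

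**The concern.** A non-inferiority claim needs evidence that the true deficit is smaller than the margin. That means rejecting a null hypothesis placed at the margin or, equivalently, showing that a confidence limit lies inside it. The protocol does neither. Its named test, on the ordinary reading, asks whether the difference is zero. Its margin rule compares an average with 2 MII as though the average were known without error.

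A reader following the text could therefore conclude non-inferiority in one of two ways: from a non-significant p-value, or from a deficit below 2. The first rewards imprecision. The second passes a tool lying exactly at the margin half the time. This decides the trial's single primary conclusion, namely whether a dosing tool is good enough to replace clinician judgement.

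**Working it through.** **Inputs.** Margin 2 MII (Trial design); SD 5.84, one-sided alpha 0.05, beta 0.2, drop-out 10%, 118 per arm (Sample size); 1:1 allocation. A true difference of 0 is assumed for power; the protocol does not state it. Differences are IDoser minus control, and a normal approximation is used.

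**Reproducing the sample size.** n = 2 × (1.645 + 0.842)² × 5.84² / 2² = 105.4 with unrounded quantiles, so 106 evaluable per arm. 106 / 0.9 = 117.8, so 118 randomised. This matches the protocol. At one-sided 2.5% the result is 134 evaluable and 149 randomised, which does not match. The trial was therefore sized at one-sided 5%.

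**Standard error.** SE = 5.84 × √(2/106) = 0.802.

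**A proper margin test.** Non-inferiority at one-sided 5% needs an observed difference above -2 + 1.645 × 0.802 = -0.68. False acceptance at a true difference of -2 is 5%. Power at a true difference of 0 is Φ(2/0.802 - 1.645) = 80.2%.

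**Point-estimate rule.** With true difference δ, the chance of escaping the inferior label is 1 - Φ((-2 - δ)/0.802).

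- δ = -2: 1 - Φ(0) = 50%
- δ = -2.5: 1 - Φ(0.623) = 27%
- δ = -3: 1 - Φ(1.247) = 11%

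**Non-significance read as non-inferiority, at δ = -2.**

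- Two-sided 5%: IDoser is significantly worse below -1.96 × 0.802 = -1.57. The chance of missing this is 1 - Φ((2 - 1.572)/0.802) = 29.7%.
- One-sided 5%: the cut-off is -1.645 × 0.802 = -1.32, and the chance of missing it is 19.8%.

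**Where the rules disagree (two-sided reading).**

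| Observed deficit (MII) | Difference test | Point rule | Margin test |
|---|---|---|---|
| 0.68 to 1.57 | not significant | not inferior | non-inferiority not shown |
| 1.57 to 2 | significantly worse | not inferior | non-inferiority not shown |

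**Sidedness.** If p < 0.05 is carried over as a two-sided 95% interval, power with 106 per arm is Φ(2/0.802 - 1.960) = 70.3%.

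**If all 118 per arm are analysed.** The protocol is not clear on this: section {11b} keeps withdrawn patients' data, while {20c} describes a per-protocol strategy. With 118, SE = 0.760 and the results are as follows.

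- Margin test: cut-off -0.75, power 83.8%.
- Point rule: 50%, 26% and 9% at true deficits of 2, 2.5 and 3.
- Non-significance at a true deficit of 2: 25% two-sided, 16% one-sided.
- Power with a 95% interval: 74.9%.

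**The case against.** Five points can be made for the protocol.

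- **The null value is not written down.** A t test can be run against a shifted null, and Trial design says that non-inferiority is what will be tested. This is true. But the same tests are applied to FSH dose and COC number, which have no margin, so zero is the natural reading, and no shifted null appears anywhere.
- **The Trial design sentence might define the margin for true means.** It does not use the word observed, and it says when IDoser is inferior, not when it is non-inferior. That reading is possible, but the wording is that of a decision rule and no other rule is given. The 50%, 27% and 11% figures depend on reading it as one and taking its complement as success.
- **No text says that a non-significant result means non-inferiority.** This is correct. The 30% and 20% figures are conditional on that reading.
- **The sample size is worded as detecting a difference.** A one-sided difference calculation also gives 106, because the two formulas coincide when the true difference is 0. However, Background and rationale links the smaller sample to the non-inferiority design. The literal wording would not rescue the plan either: the risk of passing a tool that is 2 MII worse would then be beta, about 20%, and not alpha, 5%.
- **An unseen analysis plan may settle this.** The article is not silent, though. It fixes a test, a significance criterion and a decision rule. A plan that compared a confidence limit with the margin would have to replace that published rule.

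These points limit how firmly individual figures can be stated. None supplies the missing comparison of a confidence limit with 2 MII.

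**Conclusion.** The concern holds: the primary analysis is wrong as written and must be fixed. Nowhere does the protocol compare a confidence limit with the 2-MII margin, and the rules it does state would not control the error that a non-inferiority trial exists to control. At a true deficit of 2 MII, false acceptance is 50% under the point-estimate rule, and 30% or 20% if non-significance is taken as success, against the intended 5%.

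These figures rest on the protocol's SD, 106 evaluable per arm and a normal approximation; analysing all 118 changes them little. The Mann-Whitney fallback adds to the mismatch, because its p-value gives no limit for the difference in means on which the margin is defined. The sample size of 118 per arm is not in error. The unstated side in the analysis section is an ambiguity and not a contradiction, but a two-sided 95% reading would leave power at about 70% to 75%.

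**What to change.** Reword two paragraphs.

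1. **Univariable analysis.** For the primary outcome, replace the difference test with a test of H0: mean MII (IDoser minus control) ≤ -2, at one-sided 5%. Declare non-inferiority only if the lower limit of the two-sided 90% confidence interval for the difference in means lies above -2. Remove Mann-Whitney as a substitute primary analysis; it may stay as a supporting comparison.
2. **Trial design.** Delete the rule based on the average alone. State that failing to show non-inferiority is not proof of inferiority.

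Sample size {14} should also say that 2 MII is the margin and that the true difference is assumed to be 0.

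This needs no extra patients or data: 118 per arm stands, with 80% power at 106 evaluable. If a two-sided 95% interval is preferred, either restate power as about 70% with 106 evaluable, or re-size to 134 evaluable and 149 randomised per arm.

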### Outcomes {12}

The primary efficacy criterion will be the number of mature, MII oocytes retrieved at OPU. This treatment outcome is the closest to the intervention and has a clear impact on IVF/ICSI cycle success. Secondary efficacy endpoints will include cycle cancelations (due to poor response or in the event that no mature oocytes are retrieved), OHSS risk, clinical pregnancy, and live birth per first transfer.

The following variables will be analyzed:Demographic variablesAge of the patient (years)AFCBMI (kg/m$$^2$$)AMH (ng/ml)Center of treatmentCOS outcome variablesNumber of MII oocytesNumber of cumulus-oocyte complexes (COCs)Estradiol at last ultrasound assessment (pg/ml)Number of follicles $$\ge$$ 11mm at last ultrasound checkOHSS risk ([yes/no]; risk is considered as present if estradiol > 5000 pg/ml and or $$\ge$$ 18 follicles $$\ge$$ 11mm at last ultrasound check)OPU cancelation ([yes/no]; present if COS is stopped prior to OPU)Cycle cancelation ([yes/no]; present if no MII oocytes are retrieved at OPU)Pregnancy outcome variablesClinical pregnancy ([yes/no]; present if positive fetal heart beat is observed at 7th week of gestation) per first embryo transferLive birth per first embryo transfer ([yes/no])

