**Assessments:**							
***Baseline variables***	✕	✕					
***Outcome variables***				✕	✕	✕	✕

A detailed description of the timepoints reflected in the figure is as follows:$$-t_1$$: First appointment with the clinician where information on IVF/ICSI treatment is relayed to the patient. Information on the trial is communicated to the patient, and informed consent documentation is handed over to eligible patients. If any of the baseline variables needed for IDoser to function (age, BMI, AFC, and AMH) are not available at this time, steps are put in place to obtain relevant information for the next appointment. These can include petition of blood tests for AMH level results, or echography for AFC assessment.$$t_0$$: Appointment with the clinician where the signed informed consent form is retrieved. Patient is included if all baseline variables are available. Once included, the participant is allocated to either the IDoser FSH selection group or control group. The FSH dose is prescribed to the participant.$$t_1$$: First day of the COS protocol. Participant will self-administer the prescribed dose of FSH.$$t_2$$: Last ultrasound appointment prior to OPU. First outcome variables are registered (OHSS risk and OPU cancelation).$$t_3$$: Day of OPU. Further outcome variables are registered (number of COCs recovered, number of MII recovered and cancelation after OPU).$$t_4$$: Appointment to evaluate the presence of a fetal heart beat at the 7th week of gestation to establish whether pregnancy is achieved after first embryo transfer in current IVF/ICSI cycle. Presence or absence of clinical pregnancy is registered.$$t_5$$: End of study, considered after outcome on live birth after first embryo transfer is obtained. Presence or absence of live birth achieved is registered.Baseline variables include all necessary variables required for IDoser, including age of the patient, BMI, AFC, and AMH levels.

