## Assignment of interventions: allocation

### Sequence generation {16a}

Stratified block randomization will be carried out depending on whether the patient is expected to be a poor responder (AMH < 1.2 ng/ml and AFC < 5, as per POSEIDON criteria [15]), high responder (AMH $$\ge$$ 3 ng/ml and AFC $$\ge$$ 15), or expected normo responder (any other case). This will ensure equal distribution of these patient etiologies across both arms. There will be 3 blocks (one for each strata) for every arm. The size of every block has been determined by the population distribution of each mentioned strata during the development and validation of the IDoser to be studied (13$$\%$$ poor, 15$$\%$$ high and 72$$\%$$ normo-responders) [11]. These figures translate to 15 patients in the poor responders group, 18 in the high responders, and 85 in the normo-responders within each arm. The study group (treatment or control) will be randomly assigned using a computer program with a 1:1 allocation ratio.

The 3 randomization lists will be generated using the online software Graphpad (http://www.graphpad.com/quickcalcs/randMenu/). This is a single-blinded trial, in which the patients are blinded to the source of the dose prescribed. Other clinicians apart from the one assigned to the participant, embryologists and part of the research team will also be blinded.

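### Free improvement: the primary MII comparison uses neither the randomisation strata nor the four mandatory baselines, so a valid test is conservative and leaves precision unused

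*Protocol article*

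**What the plan says.** Outcomes {12} sets the endpoint: "The primary efficacy criterion will be the number of mature, MII oocytes retrieved at OPU".

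Under Univariable analysis in the statistical methods {20a}, "Differences regarding the number of MII oocytes amongst the groups will be evaluated using" Student's t test, or Mann-Whitney U if the distribution is not normal. No stratum or covariate term is named. The same section ties the error rate to this comparison: "Alpha risk is set at a 5% for the primary analysis, focusing on the difference between MII oocytes retrieved between the two arms". It mentions adjustment only for other analyses: "For secondary and subgroup analysis, appropriate statistical adjustment methods will be implemented".

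The design collects more than the test uses. From Sequence generation {16a}: "Stratified block randomization will be carried out depending on whether the patient is expected to be a poor responder", a high responder or a normo-responder, with the classes defined by AMH and AFC. The planned sizes are "15 patients in the poor responders group, 18 in the high responders, and 85 in the normo-responders within each arm". In the participant timeline {13}, "Patient is included if all baseline variables are available", and "Baseline variables include all necessary variables required for IDoser, including age of the patient, BMI, AFC, and AMH levels". Section {20c} makes a missing covariate a reason for exclusion. The background {6a} names the same four variables as IDoser's predictors. The strata return only as subgroups, in {20b}.

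**The concern.** When allocation is balanced within strata, differences between strata largely cancel from the arm difference. A two-sample t test still counts that variation in its standard error. The estimated error is then larger than the true one, and the test rejects less often than its nominal level. Separately, variance explained by baselines that are not stratified stays in both the true and the estimated error unless the analysis adjusts for it.

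At stake is the chance of showing non-inferiority when it holds, and the sharpness of the estimate set against a margin of 2 MII. Every variable needed is complete by design, so the plan could have this precision without further patients or data.

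**Working it through.** **Inputs from the document.** Margin 2 MII (Trial design {8}). SD 5.84, one-sided alpha 0.05, power 0.80, dropout 10%, 118 per group (Sample size {14}). Strata of 13% poor, 72% normo and 15% high responders ({16a}).

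**Input that is assumed.** R², the share of MII variance explained by strata or baselines. The document gives none; 10% to 40% is used here. For orientation, hypothetical stratum means (poor/normo/high) of 4/8/12 up to 3/8/15 MII with the 13/72/15% split give between-stratum variances of 4.47 and 10.44. Divided by 5.84² = 34.11, these are R² of 0.13 and 0.31. The means are illustrative and not taken from the document.

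**1. The plan's own figure.** n per arm = 2 × (1.645 + 0.842)² × 5.84² / 2² = 105.4, so 106. Allowing for dropout, 106 / 0.9 = 117.8, so 118. This matches exactly and uses the unadjusted SD.

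**2. Planned test with R² = 0.** SE = 5.84 × √(2/106) = 0.802. Power = Φ(2/0.802 − 1.645) = 80.2%.

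**3. Variance explained by balanced strata.** The true SE is 0.802 × √(1 − R²), but the t test still uses about 0.802.

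- Unadjusted power = Φ((2/0.802 − 1.645) / √(1 − R²))
- Adjusted power = Φ(2 / (0.802 × √(1 − R²)) − 1.645)
- True one-sided error of the unadjusted test = 1 − Φ(1.645 / √(1 − R²))

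| R² of strata | Power, unadjusted | Power, adjusted | True error, unadjusted |
|---|---|---|---|
| 0.20 | 83% | 87% | 3.3% |
| 0.30 | 84% | 91% | 2.5% |

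The gain here is about 4 to 6 percentage points, because stratified allocation has already delivered part of the benefit.

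**4. Variance explained by non-stratified baselines.** The unadjusted test stays at about 80%, and adjustment has its full effect. The last column is 1.645 × 5.84 × √(1 − R²) × √(2/106).

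| R² | Residual SD | Power, adjusted | 90% CI half-width (MII) |
|---|---|---|---|
| 0 | 5.84 | 80.2% | 1.32 |
| 0.10 | 5.54 | 83.7% | 1.25 |
| 0.20 | 5.22 | 87.3% | 1.18 |
| 0.30 | 4.89 | 90.9% | 1.10 |
| 0.40 | 4.52 | 94.2% | 1.02 |

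**5. Simulation.** 8,000 runs, 106 per arm, arms balanced within strata. Strata explained 10% or 20% of variance, and one further covariate 10% or 20%. The unadjusted t test had a true one-sided error of 3.3% to 3.7% and power of 81% to 83%. The linear model with stratum and covariate had an error of 4.7% to 5.1% and power of 87% to 94%. This agrees with steps 3 and 4.

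All these figures are for the t test. The Mann-Whitney branch was not evaluated.

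**The case against.** The strongest reply is that nothing is broken. N was set on the unadjusted SD and the planned test is unadjusted, so the plan is consistent with itself. Its error rate is at or below nominal, and in a non-inferiority trial that is the safe direction. All of this stands.

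A reader might infer three stronger claims, and the document supports none of them.

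- *The trial is underpowered by this choice.* It is not; step 1 reproduces its 80% power.
- *Chance imbalance in age, BMI or centre biases the result.* The randomised difference is unbiased, and its standard error already allows for such imbalance. Adjustment would narrow that error; it does not repair a bias.
- *Power moves from 80% to 94% whatever the source of explained variance.* For the stratum part the comparator is about 83% or 84%, because balanced stratification has already lowered the true error.

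The size can also be questioned. Both arms choose the dose from these same variables, and IDoser steers patients towards a target range, which may weaken the remaining link between baselines and MII. No R² in the document settles this. The step 3 figures also assume that arms stay balanced within strata at analysis.

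One might add that covariates are commonly left to an analysis plan. Here, however, the article names the primary test, and its promise of adjustment reaches only secondary and subgroup analyses. That phrase could mean covariates or multiplicity; either way it does not cover the primary comparison. Whether the named tests are set against the margin at all is a separate question and adds no weight to this one.

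**Conclusion.** The point holds as a free improvement. The primary MII comparison uses neither the randomisation strata nor the complete baselines. The t test as planned is valid, somewhat conservative and powered as stated, so a positive result from it would stand. The cost is forgone power: about 4 to 6 points if strata explain 20% to 30% of variance, and about 4 to 14 points if non-stratified baselines explain 10% to 40%. The plan describes no interval for the primary comparison, so the half-widths show what an interval would gain and do not describe a fault in a stated one. The direction is secure as long as the strata and baselines are related to MII yield. The size rests wholly on assumed R² values.

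**What to change.** Prespecify, before outcome data are seen, that the primary estimate is the arm coefficient from a linear model of MII count on arm, randomisation stratum, age, BMI, AMH and AFC, with robust standard errors. Centre may be added; it is already recorded. Judge the one-sided 95% confidence limit of the adjusted mean difference (the lower limit of a two-sided 90% interval) against the 2-MII margin. Keep N at 236, and report the unadjusted difference as supportive.

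Stratum is defined from AMH and AFC, so it overlaps with them. This does not harm the arm coefficient.

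Binary secondary outcomes can likewise be reported as stratum-adjusted risk differences with confidence intervals, for example Mantel-Haenszel. The article already promises unspecified adjustment for secondary and subgroup analyses, so this would only say what is meant.

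The cost is analysis wording and a few degrees of freedom out of about 212 evaluable participants. No patients, visits or data are added.

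### The primary MII comparison switches to Mann-Whitney if the data are not normal, although the hypothesis, margin and sample size all concern a difference in means

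*Protocol article*

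**What the plan says.** Objectives {7} asks whether IDoser is "not inferior to the performance of a clinician in the average number of mature oocytes retrieved". Trial design {8} asks whether it is "non-inferior to the standard clinical protocol in regards to the average number of mature oocytes recovered per group" and sets the margin on the same scale: "If the average number of MII in the intervention group is inferior in 2 or more units", IDoser counts as inferior.

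Sample size {14} arrives at 118 per arm to address a 2-MII difference, "accepting an alpha risk of 0.05 and a beta risk of 0.2 in a one-sided test". It adds "We estimate a mean common standard deviation of 5.84", and the authors "anticipate a drop-out rate of 10" per cent.

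The Univariable analysis section then gives the primary comparison as Student's t test or the Mann-Whitney U "test (if the distribution is not normal). These tests will also be used to compare FSH doses and COC number". A p-"value < 0.05 will be considered as statistically significant".

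Background and rationale {6a} also matters here. It lists making outcomes less variable between patients, oocyte number in particular, among the reasons for the model.

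**The concern.** Three parts of the protocol fix the quantity of interest as a difference in means. The analysis section then lets the observed distribution decide whether that quantity is tested at all. The t test leads directly to a confidence limit for the mean difference, which can be set against -2. Mann-Whitney concerns how the two distributions are ordered, and its p-value is not a statement about a mean deficit of 2 MII.

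What is at stake is the trial's only primary conclusion. The non-inferiority verdict could depend on which branch a normality check selects. On the rank branch, a pass would not carry the meaning that Trial design {8} gives it.

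**Working it through.** **Inputs from the protocol.** Margin 2 MII, SD 5.84, one-sided alpha 0.05, power 0.80 and drop-out 10% (Trial design {8}, Sample size {14}); 1:1 allocation. **Assumed, because the protocol does not give them:** mean MII of 7 to 12, the shape of the distribution, and the SD in the IDoser arm.

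**1. The stated sample size is a means calculation.** With a true difference of zero,

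n per arm = 2 × SD² × (z₀.₉₅ + z₀.₈₀)² / margin² = 2 × 5.84² × (1.6449 + 0.8416)² / 2² = 68.2112 × 6.1827 / 4 = 105.4, so 106.

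Allowing for drop-out: 106 / 0.90 = 117.8, so 118. The plan's figure is reproduced exactly. Power at 106 per arm is 0.802.

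**2. What each test examines.** Write T for IDoser and C for control.

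- Margin-based t test: null hypothesis mean(T) − mean(C) ≤ −2.
- Mann-Whitney on counts shifted by 2: null hypothesis P(T + 2 > C) + ½P(T + 2 = C) ≤ ½.

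The two agree at the margin if T + 2 and C have the same distribution, that is, if IDoser moves the counts without changing their shape. Suppose instead that counts are right-skewed and the IDoser arm is less spread. The longer control tail then raises the control mean more than it raises a typical control value. At a mean deficit of exactly 2, a shifted IDoser count then exceeds a control count more than half the time, and the rank test leans towards declaring non-inferiority.

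**3. Size of the effect at the margin.** Simulation with 106 per arm, negative binomial counts, a true mean deficit of exactly 2 and 3,000 trials per row. Entries are the proportion of trials declaring non-inferiority at one-sided 5%, with 2 added to the IDoser counts. The simulation error is about √(0.05 × 0.95 / 3000) = 0.4 percentage points at 5%.

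| Control mean, SD | IDoser mean, SD | t test | Mann-Whitney |
|---|---|---|---|
| 9, 5.84 | 7, 5.84 | 4.6% | 3.4% |
| 10, 5.84 | 8, 5.84 | 4.6% | 4.0% |
| 9, 5.84 | 7, 4.5 | 5.4% | 14.8% |
| 9, 5.84 | 7, 4.0 | 6.0% | 21.5% |
| 10, 5.84 | 8, 4.5 | 5.6% | 13.0% |
| 10, 5.84 | 8, 4.0 | 5.6% | 18.3% |
| 12, 5.84 | 10, 4.5 | 5.2% | 11.1% |

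A separate run with the Welch test gave 5% to 6% for Welch and 11% to 21% for the shifted Mann-Whitney in the unequal-SD settings.

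**4. How often the fallback would be used.** Proportion of 1,000 simulated trials in which normality is rejected at 5% in at least one arm (SD 5.84, 106 per arm). The clipped-normal model uses normal values rounded and cut off at zero.

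| Assumed mean | Negative binomial, Shapiro-Wilk | Negative binomial, D'Agostino | Clipped normal, Shapiro-Wilk | Clipped normal, D'Agostino |
|---|---|---|---|---|
| 7 | 100% | 100% | 100% | 76% |
| 8 | 100% | 100% | 100% | 55% |
| 9 | 100% | 100% | 96% | 41% |
| 10 | 100% | 99% | 67% | 26% |
| 12 | 99% | 93% | 22% | 13% |

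The fallback is likely if counts are right-skewed, but its frequency depends on things the protocol does not state.

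**The case against.** The best defence is that a rank test can respect the margin. Mann-Whitney on counts shifted by 2, or a Hodges-Lehmann limit compared with -2, addresses a 2-unit location shift when the arms have the same shape. In that case it performs well: with equal SDs its error at the margin is 3.4% to 4.0%, and with no true difference at mean 9 its power is 86% against 80% for the t test. How the margin enters the test is also a detail that an analysis plan not shown here could hold. This stands, so it would be wrong to say that no rank test could ever address the margin. It does not rescue the rule in this trial, because equal shape is the condition that the model's own aim of reducing variability undermines.

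A reader might also infer that the normality check is bound to fail, so that Mann-Whitney is the primary test in practice. The documents do not support that. They give no mean MII, distribution, normality test or cut-off, and step 4 shows rates from 13% to 100% according to what is assumed.

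A third tempting reading starts from a constructed case in which IDoser caps every response at 10 in a population with mean 10, giving a mean deficit of 2.28. There an unshifted Mann-Whitney is non-significant in 33% of trials against 3.5% for Welch. These are superiority tests, and the figures matter only if non-significance is read as non-inferiority, which is not the rule in Trial design {8}. An unshifted t test has the same fault: at a deficit of exactly 2 it is non-significant in 16% to 31% of the simulated trials. The cap is also extreme, since it sits at the lower end of the model's own 10 to 15 oocyte target. Those figures do not measure the effect of the switch.

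**Conclusion.** The point holds as a mismatch between the stated analysis rule and the stated hypothesis. One branch of the primary analysis does not test the difference in average MII on which the objective, margin and sample size rest. That is so however often the branch is taken, and an analysis plan that followed the rule would inherit the problem.

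Its practical size is conditional. If the rank branch is used with the margin built in, the false non-inferiority rate is roughly two to four times the nominal 5% in the unequal-SD settings examined. That rests on assumed negative binomial counts, control means of 9 to 12 and an IDoser SD of 4.0 to 4.5. If the arms have equal spread, there is no inflation. The mean-based test stays close to its nominal level in all these settings, so skewness gives no reason for a switch at this sample size.

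**What to change.** Remove the normality-dependent choice for the primary outcome. State instead that the difference in mean MII (IDoser minus control) will always be estimated, by Welch's method or a linear model with robust standard errors, and that non-inferiority is concluded if the one-sided 95% lower confidence limit (the lower limit of the two-sided 90% interval) lies above -2. Keep Mann-Whitney as a supportive analysis only. A bootstrap interval for the mean difference is an optional check for skewness.

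The cost is wording in the protocol and analysis plan, with the approval that the protocol requires for any amendment. No new data are needed, and the sample size does not change. Trial status describes recruitment as not yet begun; in any case the change should be made before outcomes are compared by arm.
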